### Outcomes

#### Primary outcome

The primary outcome will be the change in HbA1c levels at 6 months in the FEEDBACK intervention group compared with the control group. HbA1c levels will be derived from the samples collected by venepuncture at baseline, 3 months, and 6 months, obtained by the NGSP (National Glycohaemoglobin Standardisation Programme) certified method.

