#### Primary analyses for primary and secondary outcomes

The planned primary analyses will be carried out at the individual level, according to the intention-to-treat (ITT) principle. Between-group comparisons will be analysed using multilevel analysis to account for the dependency of observations. Between-group differences in the mean changes in primary and secondary outcomes will be estimated using linear mixed-effects models for continuous outcomes and logistic mixed-effects models for binary outcomes. Random effects will account for within-practice clustering and within-patient correlation. Fixed effects will be treatment group indicator (with the control group as the reference category), practice size (stratification variable) [68] and, where relevant, time indicators, their interaction effects, and baseline values of variables identified as potential confounders. In case normality assumptions are violated, outcome variables will be log-transformed and, if necessary, non-parametric tests will be used. Data analyses will be performed using Stata/MP 17 (StataCorp).

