### Sample size

Assuming individual randomisation, recruitment of at least 76 participants per arm would be required to achieve 80% power with type I error α=0.05. These calculations have assumed the detection of a clinically meaningful difference of 0.5% (5.5 mmol/mol) in change in HbA1c between the two arms [71] and standard deviation of 1.1% (12 mmol/mol) based on a previous study with comparable population [72]. However, this sample size needs to be inflated to account for clustering effects and potential dropouts. Therefore, the final sample size will be adjusted according to the final number of clusters, the cluster average size, the estimated intra-class correlation coefficient (ICC), and the expected drop-out rate.

A systematic search of ICCs used in the design of cluster RCTs in T2DM with HbA1c as primary (continuous) outcome found that the median value used in published trials was 0.047 [73]. However, recent studies investigating the actual ICCs from large primary care datasets reported values comprised between 0.02 and 0.032 for HbA1c [74], suggesting that ICCs used in sample size calculation for cluster RCTs tend to be over conservative. Assuming an ICC of 0.035 and accounting for potential variations in cluster size, the effective sample size required to detect a 0.5% difference in HbA1c and to achieve 80% power with type I error α=0.05 is 119 participants per group. These calculations have assumed the mean cluster size to be 15 with standard deviation of 5, yielding a coefficient of variation of 0.33 and a design effect of 1.55 [75]. Moreover, assuming 10% loss to follow-up, 264 participants in total will be needed.

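### The non-normality fallback covers the primary outcome without fixing a scale that can be logged or requiring a non-parametric test that respects practice clustering

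*Protocol article*

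**What the plan says.** The rule stands in the Protocol article under Primary analyses for primary and secondary outcomes. That section first states the general approach: "Between-group comparisons will be analysed using multilevel analysis to account for the dependency of observations". It then names the effect measure and model: "Between-group differences in the mean changes in primary and secondary outcomes will be estimated using linear mixed-effects models for continuous outcomes". On dependence it adds: "Random effects will account for within-practice clustering and within-patient correlation". Fixed effects are treatment group, practice size and, "where relevant, time indicators, their interaction effects, and baseline values of variables identified as potential confounders".

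The fallback follows: "In case normality assumptions are violated, outcome variables will be log-transformed and, if necessary, non-parametric tests will be used". It is not limited to secondary outcomes, and the section heading covers both kinds.

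The Primary outcome section defines what is analysed: "The primary outcome will be the change in HbA1c levels at 6 months in the FEEDBACK intervention group compared with the control group". The Sample size section powers the trial for "detection of a clinically meaningful difference of 0.5% (5.5 mmol/mol) in change in HbA1c between the two arms".

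**The concern.** The fallback has two steps, and each can part company with the design.

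- **Log step.** Taken at face value, the primary outcome variable is a change, and the trial hopes it is negative. Zero and negative values have no logarithm. If the log is applied to HbA1c levels instead, the treatment effect becomes a ratio, and a given absolute difference corresponds to different ratios at different starting levels.
- **Non-parametric step.** The move is from mixed models to tests. An ordinary rank test has no practice effect, no practice-size term and no repeated-measures structure. Practices are the randomised units, so a test that treats patients as independent understates the variance.

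Later analyses also depend on the primary model. The Sensitivity analyses section rests its missing-at-random argument on that approach and applies offsets to a mean outcome. The Subgroup analyses section refits the same model. A rank test supplies neither a model nor a mean difference. Finally, which analysis is primary would depend on how the outcome data look.

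**Working it through.** **Inputs from the Sample size section:** difference 0.5; SD 1.1; α = 0.05; power 80%; ICC 0.035 for planning, 0.02 to 0.032 from primary care datasets and 0.047 as the median in published trials; mean cluster size 15, SD 5, coefficient of variation (CV) 0.33; design effect (DE) 1.55; 119 per group; 264 in total; 20 practices. Sidedness is not stated. I assume two-sided because it reproduces the plan's figure (one-sided would give 60 per arm).

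**1. The plan's own figures.**
- Individual randomisation: n = 2 × [1.1 × (1.960 + 0.842) / 0.5]² = 76 per arm. This agrees with "recruitment of at least 76 participants per arm would be required to achieve 80% power with type I error α=0.05".
- DE = 1 + [(1 + CV²) × m − 1] × ICC = 1 + [(1 + 0.33²) × 15 − 1] × 0.035 = 1.547, stated as 1.55.
- 76 × 1.55 = 118 per group against 119 stated; 238 / 0.9 = 265 against 264 stated. Both are within rounding.

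**2. Can the change score be logged?** Take 1.1 as the SD of the change and assume a normal distribution. The mean change is not given, so I vary it. P(change ≤ 0) = Φ(−mean / 1.1):

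| Assumed mean change | Share at or below zero |
|---|---|
| 0 | 0.50 |
| −0.25 | 0.59 |
| −0.5 | 0.68 |
| −1.0 | 0.82 |

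Reversing the sign, so that a reduction is positive, does not rescue the step: at a mean reduction of 0.5, 1 − 0.68 = 0.32 of patients would still be at or below zero.

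**3. Logging levels instead.** Levels are positive, so this can be computed. The effect is then a ratio. A fall of 0.5 points from 7.0 is 6.5 / 7.0 = 0.929; from 8.0 it is 7.5 / 8.0 = 0.938. No single ratio corresponds to the planned 0.5-point difference.

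**4. Type I error of a test that ignores practices.** With no true effect, the error is about 2 × [1 − Φ(1.96 / √DE)].

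| ICC | m | DE | Type I error |
|---|---|---|---|
| 0.035 | 15 | 1.547 | 0.115 |
| 0.035 | 13.2 (264 / 20) | 1.477 | 0.107 |
| 0.035 | 11.9 (238 / 20) | 1.427 | 0.101 |
| 0.02 | 11.9 | 1.244 | 0.079 |
| 0.047 | 15 | 1.735 | 0.137 |

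At the planning values the error is 0.115 / 0.05 = 2.3 times nominal; at the lowest row it is 0.079 / 0.05 = 1.6 times.

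**5. Simulation check.** Null data, 20 practices paired by size, mean size 13.2, ICC 0.035, 3,000 runs per setting. The individual-level rank-sum test rejected in 0.102 of runs with normal errors and 0.123 with skewed errors. Over ICCs 0.02 to 0.047 the rates ran from 0.091 to 0.115 (normal) and 0.093 to 0.143 (skewed). A rank test on practice means, in the same simulations, stayed at about 0.04 to 0.05.

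**The case against.** The strongest reply is that the protocol prescribes neither fault.

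- **The log.** The text speaks of outcome variables in general. A model with patient-level correlation, time indicators and interactions can be fitted to HbA1c levels at baseline, 3 and 6 months, with the change estimated as a group-by-time term. Levels can be logged. So a reader who infers that the first step cannot be computed goes further than the text allows. This stands; what remains is that the scale is open and that the loggable reading gives up the planned effect measure.
- **The test.** No test is named, and the same paragraph commits to handling dependence. Practice-level rank tests, permutation tests and clustered rank-sum tests are all non-parametric. A rank method can also give a shift estimate in HbA1c units (Hodges-Lehmann). A reader might infer that the plan mandates an unclustered test; it does not. This also stands. But the paragraph implements its commitment through random effects, which an ordinary rank test lacks, and it places the primary analyses at patient level. Nothing carries the commitment over to the fallback.
- **Detail for the SAP.** The trigger and the name of the test may properly be settled there, and their absence is not the point. The point is that a stated rule reaches the primary outcome, and a later plan would have to override it.
- **Likelihood.** With about 119 patients per arm, a mean difference tolerates moderate non-normality, so the last step may never be reached for HbA1c. The sentence may have been written mainly for skewed secondary outcomes. This is fair and lowers the severity. It also argues for removing the primary outcome from the rule.

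**Conclusion.** The concern holds as a badly fixed rule. The fallback extends to the primary outcome, leaves open a scale on which the log is often undefined or no longer answers the planned question, and does not require the non-parametric test to respect practice clustering.

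If an ordinary individual-level rank test were used, its type I error would be about 0.115 at the planning values and about 0.08 to 0.14 over the quoted ICCs. This assumes two-sided α of 0.05, cluster sizes of about 12 to 15 with CV 0.33, and 20 practices. It would be wrong to read this as the trial's error rate having doubled: it applies only if normality is judged violated, the log is judged inadequate and an unclustered test is chosen. Nor should the figure be worsened by assuming 10 practices. In the Sample size section that number marks when patient recruitment begins; the enrolment target is 20.

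The shares of non-positive changes rest on an assumed normal distribution and assumed mean changes from 0 to −1.0. Severity is moderate: it should be corrected before the final analysis, but the planned mixed model itself is not in question.

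**What to change.** Replace the fallback sentence with a rule in three parts.

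1. **Primary outcome.** The linear mixed model on untransformed HbA1c remains the primary analysis whatever the residual distribution. This keeps the effect in percentage points and leaves the sensitivity and subgroup analyses attached to the same model.
2. **Robustness check.** Pre-specify one method that follows the randomisation, for example a permutation test that re-allocates practices within the size strata, or a practice-level bootstrap interval. With 20 practices in strata of two, as the Randomisation section describes, there are 2¹⁰ = 1,024 possible allocations, enough for a usable permutation p-value.
3. **Other outcomes.** Log only strictly positive level outcomes, such as the CHD probability itself and not its change, and report the effect as a ratio. Require any non-parametric test to respect practice clustering.

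The cost is a few sentences and a few lines of analysis code. No data collection, sample size or trial procedure changes. The wording should be settled before the outcome data are analysed.

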#### Sensitivity analyses

Sensitivity analyses will be carried out to evaluate the robustness of the estimated intervention effect on the primary outcome based on differing missing data assumptions. While our primary analytic approach can provide unbiased estimates under the assumption that data are missing at random, we will examine the sensitivity of statistical inferences to data being missing not at random, i.e. to cases where missingness depends on the unobserved values even after controlling for predictive variables. We will do so using a pattern-mixture model (PMM) approach, which assumes that participants who drop out have a mean outcome that deviates from that of participants who do not drop out by a given offset, and then explores the effect on the findings of various clinically realistic values of this offset (best case and worst-case scenarios) in the two study groups [69, 70].

#### Subgroup analyses

In addition, the ITT model for the primary outcome will be fitted for the following subgroups of interest: (1) including only patients with HbA1c > 8.0% at baseline to examine the effects of the FEEDBACK intervention on poorly controlled patients; (2) by duration of diabetes; (3) by age and sex; (4) by objective numeracy level; (5) by level of intention to change behaviour at baseline.

### Sample size

Assuming individual randomisation, recruitment of at least 76 participants per arm would be required to achieve 80% power with type I error α=0.05. These calculations have assumed the detection of a clinically meaningful difference of 0.5% (5.5 mmol/mol) in change in HbA1c between the two arms [71] and standard deviation of 1.1% (12 mmol/mol) based on a previous study with comparable population [72]. However, this sample size needs to be inflated to account for clustering effects and potential dropouts. Therefore, the final sample size will be adjusted according to the final number of clusters, the cluster average size, the estimated intra-class correlation coefficient (ICC), and the expected drop-out rate.

A systematic search of ICCs used in the design of cluster RCTs in T2DM with HbA1c as primary (continuous) outcome found that the median value used in published trials was 0.047 [73]. However, recent studies investigating the actual ICCs from large primary care datasets reported values comprised between 0.02 and 0.032 for HbA1c [74], suggesting that ICCs used in sample size calculation for cluster RCTs tend to be over conservative. Assuming an ICC of 0.035 and accounting for potential variations in cluster size, the effective sample size required to detect a 0.5% difference in HbA1c and to achieve 80% power with type I error α=0.05 is 119 participants per group. These calculations have assumed the mean cluster size to be 15 with standard deviation of 5, yielding a coefficient of variation of 0.33 and a design effect of 1.55 [75]. Moreover, assuming 10% loss to follow-up, 264 participants in total will be needed.

Based on these calculations, we aim to enrol 20 practices in the study. After 10 practices are enrolled (the inclusion of a minimum of 10 clusters is recommended, otherwise it is difficult to maintain both an appropriate type I error and sufficient power, even when small-sample correction methods are applied [76]), each practice will proceed with the recruitment of eligible patients. Two months after the start of the recruitment process, we will carry out a first assessment of each cluster size, calculate the coefficient of variation, and determine whether the total number of enrolled participants is sufficient according to the updated sample size calculation. Should this number be too small in view of the required sample size, we will recruit additional clusters until an effective sample size is reached, as long as our budget constraints permit it. In the unlikely event that additional practices cannot be recruited, or that the coefficient of variation in cluster size turns out to be much higher than expected (making the effective sample size too big given our budget constraint), we will consider opting for a cluster design with providers, rather than practices, as the unit of randomisation.

### Intervention fidelity

A standardised training protocol will be developed to minimise variability and maintain intervention protocol fidelity across all practices. GPs participating in the study will receive training consisting of a video featuring a mock consultation, delivered by a member of the research team to ensure that each step of the FEEDBACK intervention (or its control counterpart) is understood and appropriately followed. The members of the practice staff in charge of data collection will also receive instructions on how to properly fill out the standardised forms. Before the start of the trial, the intervention will be piloted in each practice allocated to the intervention group. We will assess the acceptability of the intervention and the feasibility of the data collection process. Should they be required, adjustments to the study procedures will be made.

### Confidentiality

In order to ensure data anonymity, practice and participant ID numbers will be used to combine datasets (baseline and follow-up measures) and to identify participants who withdraw from the study. The research team will not have access to the files enabling to match individual participants to their ID numbers. Participant data (i.e. consent forms, questionnaires, data extracted from practice records) will be stored in a locked cabinet in a researcher’s office. All data will be destroyed by the research team within 5 years after publication.

### Trial management

The study has two oversight committees:Trial Steering Committee (TSC)

This group is composed of the Principal Investigator, Co-Principal Investigator, study statistician, sponsor’s representative, and two members who are completely independent of the study. The TSC plays a critical role in providing strategic oversight and executive decision-making power in relation to the conduct of the study.Trial Management Team (TMT)

The day-to-day running of the trial will be overseen by a group chaired by the Principal Investigator and comprising of the data collection team and the partners of participating GP practices. This group will convene every two weeks to review the trial's progress, discuss any issues that have arisen, and ensure the smooth operation of the trial.

### Data monitoring

Due to the low-risk nature of the intervention, the short duration of the trial, and the fact that interim analyses may not provide necessarily informative results given the nature of the study, there will be no Data Monitoring Committee. The research team will comply with data collection and management procedures approved by the research ethics committee of Kashima Hospital, Fukushima, Japan, and abide by the rules of medical confidentiality.

### Harms

There is no anticipated harm resulting from participation in the trial, and participants will not receive compensation for their involvement. Nevertheless, some participants may express higher emotional response to CV risk communication than others. As emotional response to CV risk score is one of the secondary outcome measures, we will be able identify such participants and inform GPs to make sure that no unnecessary anxiety is triggered as a result of study participation. Should the study provide evidence of the effectiveness of the FEEDBACK intervention, we will provide access to it to study participants in the control group, to ensure they have access to the same benefits as those in the intervention group.

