***Step 5 – Continuing support***	
Communicating updated CV risks using the heart age tool	2.7. Feedback on outcome(s) of behaviour
Revising the behaviour change goal and strategy, if needed	1.5. Review behaviour goal(s)

^a^Coded according to Michie et al.’s Behavior Change Technique Taxonomy (v1) [26]

The 5C framework is rooted in the empowerment (or patient-centred) approach to care, which suggests that the patient should be at the centre of the behaviour change process [42]. As part of this approach, providers have a key role to play in fostering patient motivation and empowerment to adhere to behavioural management.

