##### Feedback

At the follow-up visit, participants’ effective heart age will be updated. If behaviour change does not meet expectations, participants and GPs will discuss whether the behaviour change goal is appropriate and if the action plan needs to be applied more rigorously, modified, or abandoned (in which case alternative strategies will be considered). Another cycle will then start from that point onwards and up to the next follow-up visit.

Overall, the intervention will be implemented during three routine visits including the baseline visit — i.e. over 6 months — and be delivered besides standard diabetes care (see below).

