##### Psychosocial outcomes

Doctor-patient communication will be evaluated using the dedicated 8-item subscale of a validated Japanese-language version of the General Practice Assessment Questionnaire (GPAQ) [55, 56] and a translated version of the 4-item ‘Ask, Understand, Remember Assessment’ (AURA) instrument [57, 58], after each visit. The GPAQ items focus on GP’s interpersonal and communication skills (patients will be asked to rate them on a scale of 1 to 6), while the AURA instrument assesses patient communication self-efficacy on a 1 to 4 scale.Participatory decision-making will be measured using a 7-item subscale of the validated Japanese-language version of the Patient Assessment of Chronic Illness Care (PACIC) scale, at baseline and at 6 months [59]. Participants will be asked how often over the past 6 months their GP performed any of six behaviours associated with participatory decision-making. The five response categories range from 0 (‘almost never’) to 5 (‘almost always’).Psychosocial self-efficacy will be measured at baseline, 3 and 6 months, using a validated Japanese-language version of the Appraisal of Diabetes Scale (ADS) [60, 61], a questionnaire developed to evaluate patients’ awareness of the psychological burden of T2DM and their ability to manage this burden. The ADS uses three subscales: four questions on the subjective impact of T2DM, two questions on the sense of self-control regarding T2DM, and one question on self-efficacy in diabetic control. Each item is rated on a 5-point Likert scale, with lower scores indicating better performance.Recall of the CV risk score (effective heart age or 5-year CHD probability) will be assessed as correct or incorrect based on open numerical responses (i.e. depending on whether or not the participant gives the exact right answer) immediately after the baseline visit, and at 3 months, immediately before the 2^nd^ visit.Emotional response to the CV risk score will be assessed by a 3-item, 7-point Likert scale, ranging from ‘not afraid/anxious/worried at all about the risk score’ to ‘very afraid/anxious/worried about the risk score’, immediately after the baseline visit [62].Perceived credibility of the CV risk score will be assessed by a 4-item (‘I felt that the number received was ‘my number’; ‘I found the number to be written personally for me’; ‘I felt that the information was relevant to me’; ‘I felt that the information was designed specifically for me’), 7-point Likert scale (from ‘completely disagree’ to ‘completely agree’) adapted from previous similar research, immediately after the baseline visit [63].Intentions to change behaviour according to the Theory of Planned Behaviour [64] will be measured using a translated version of the dedicated items of the Determinants of Lifestyle Behaviour Questionnaire (DLBQ) [65], before and after the baseline visit. Each item is associated with a different self-care activity (eating healthier, increasing physical activity, and quitting smoking) and is rated on a 5-point Likert scale, ranging from ‘strongly agree’ to ‘strongly disagree’.

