**Psychosocial outcomes**							
Doctor-patient communication							
GP communication	GPAQ [55, 56]		X		X		X
Patient communication self-efficacy	AURA [57, 58]		X		X		X
Participatory decision-making	PACIC [59]	X					X
Psychosocial self-efficacy	ADS [60, 61]	X			X		X
Recall of CV risk score	Open-ended question		X	X			
Emotional response to CV risk score	Dedicated Likert scale [62]		X				
Perceived credibility of CV risk score	Dedicated Likert scale [63]		X				
Intentions to change behaviour	DLBQ [65]	X	X				

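### The only anxiety safeguard named under Harms is measured once, after the baseline visit, so it does not cover reactions to the updated heart age given at follow-up

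*Protocol article*

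**What the plan says.** **The safeguard.** The Harms section expects no harm from taking part, but allows that some participants may respond more emotionally than others to risk communication. Its answer is: "As emotional response to CV risk score is one of the secondary outcome measures, we will be able identify such participants and inform GPs". The stated aim is "to make sure that no unnecessary anxiety is triggered as a result of study participation".

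**The measurement.** Under Psychosocial outcomes: "Emotional response to the CV risk score will be assessed by a 3-item, 7-point Likert scale". The timing given there is "immediately after the baseline visit [62" (the quote ends in the citation number). In Table 3 the row "Emotional response to CV risk score" has a single mark, in the after-visit column of the baseline visit, and nothing at 3 or 6 months.

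**The exposure.** Table 2, Step 5, lists "Communicating updated CV risks using the heart age tool". The Feedback section says: "At the follow-up visit, participants’ effective heart age will be updated". It adds: "Overall, the intervention will be implemented during three routine visits including the baseline visit". Control participants also receive a personalised risk, expressed as a 5-year probability (Control group section). The Discussion refers in general terms to three visits at which the intervention or its control counterpart is delivered.

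**The concern.** The Harms section relies on an outcome measure to find participants who are distressed by risk communication, and states its purpose for study participation as a whole. The schedule collects that measure after the first communication only.

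The later communications differ in kind from the first. At baseline nobody has yet set a goal or signed a contract. At follow-up a participant may learn that heart age is unchanged or worse after committing to an action plan, and the Feedback section provides for a discussion when behaviour change falls short of expectations. A baseline score cannot record a reaction to that message.

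Two things are at stake. The identify-and-inform step has no data to act on after the second and third visits. And any statement on emotional response in the trial report will describe the first reaction only, although repeated feedback is one of the five steps of FEEDBACK.

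**Working it through.** No sample-size, power or error-rate figure is involved, so the check compares the schedule of exposure with the schedule of measurement.

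**1. When is a risk communicated in the intervention arm?**
- Baseline: yes (Table 2, Step 1; Risk communication section).
- 3 months: yes (Feedback section; Table 2, Step 5).
- 6 months: yes on the natural reading. The Feedback section starts a new cycle that runs to the next follow-up visit and counts three delivery visits over 6 months.

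**2. When is the emotional-response scale completed?**
- Baseline, after the visit: yes.
- 3 months: no.
- 6 months: no.

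Text and Table 3 agree, so this is not a misprint in one of them.

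**3. Coverage.** One administration over three delivery visits: 1/3. If only the 3-month update is taken as certain, coverage is 1/2 and the gap remains.

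**4. What else could register later distress?**

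| Channel | When | Specific to the risk score? | Tied to the Harms procedure? |
|---|---|---|---|
| Review of depression and anxiety in standard care, both arms | At visits | No | No |
| ADS (psychological burden of diabetes) | Before the baseline visit; after the 3- and 6-month visits | No | No |
| Adverse events, as a ground on which the steering committee may stop the study | Not stated | No | No |

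Distress from the 3-month update could come up in the history taken at 6 months. No study visit is described after the 6-month update, so for that one only the ADS completed the same day remains.

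**5. Is there room to add the scale?** Table 3 already has after-visit questionnaires at 3 and 6 months: the GP communication items (GPAQ), the patient communication self-efficacy items (AURA) and the ADS. Three more items need no new contact with the participant.

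**The case against.** The strongest reply is that the Harms section and the outcome schedule do not strictly contradict each other. The Harms text says that strong responders can be identified; it does not promise a measurement after every communication. It can be read as a screen at first exposure that alerts the GP before later updates, and a single baseline administration serves that purpose. This reading is fair, and it is why the point is a gap in coverage and not an outright inconsistency. It does not help a participant who was calm at baseline and is upset by a later update, and the stated aim is not limited to the first visit.

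A second reply is that GPs see these participants face to face and are asked in both arms to follow a standard of care that includes depression and anxiety. That stands, and so does the point about the ADS. A reader might infer from the single administration that later distress cannot be detected or is never assessed; because of these two channels, the documents do not support that. What they support is narrower: the channels are non-specific, and nothing links them to the step of identifying participants and informing GPs.

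Third, comparing worry after repeated heart-age feedback with worry after repeated probability feedback is not a stated objective, and the control-group text does not spell out that the probability is given again. Both are correct. The case rests on the safeguard, not on an unanswered research question.

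Fourth, this is a condensed article, and a full protocol may hold more detailed harms procedures. That limits the claim to the safeguard named here. It does not explain the gap, because the article prints a complete outcome schedule.

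The absence of a data monitoring committee has no bearing: such a committee would not pick up one participant's anxiety after a consultation.

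**Conclusion.** The point holds in a limited form. The one safeguard named under Harms covers one of three delivery visits and cannot register a reaction to the heart age updated at follow-up. Routine history-taking and the ADS give partial, non-specific cover that the protocol does not connect to the safeguard.

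This assumes that the risk is communicated again at both follow-up visits. The 3-month update alone is enough for the conclusion.

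The size should not be overstated. One could count 264/2 = 132 participants per arm and 132 × 2 = 264 follow-up communications in the intervention arm without the scale. That is an upper bound before drop-out (the plan assumes 10% loss) and happens to equal the total sample size. It counts consultations, not distressed people. The documents give no frequency or severity of distress and none can be derived, so 264 is not a measure of harm.

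The primary outcome and its analysis are not affected. In a low-risk trial this is an inexpensive improvement that should be made, not a flaw that threatens the result.

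**What to change.** Preferred:
- In Table 3 and the Psychosocial outcomes text, add the same 3-item scale to the after-visit questionnaires at 3 and 6 months, in both arms wherever an updated risk is communicated.
- In the Harms section, state that the existing step of identifying participants and informing GPs applies after each administration.
- Report emotional response by arm at each time point.
- State in the Control group section whether the probability is communicated again at follow-up, so that it is clear where the scale applies.

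Minimum alternative: keep the single administration and limit the Harms statement to the first communication. Either way, the Harms section, the outcome schedule and the Feedback section should be reconciled.

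Cost: a little participant time, revised forms, prompt scoring and GP notification at two more visits, and possibly an ethics amendment. At the protocol date (18/01/2023) recruitment was expected to run to April 2023, and baseline visits were to start only after recruitment and randomisation were complete, so the forms could still have been changed before any follow-up visit. If follow-up visits have already taken place, the minimum alternative remains, and the report should say that emotional response was observed after the first communication only.
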